#### Incremental Cost-effectiveness Analysis

The incremental cost-effectiveness ratio (ICER) measures a ratio of costs to outcomes, with the denominator being the difference in costs between the intervention and control groups, and the numerator being the difference between these groups in an outcome measure. The primary analysis will compute the ICER for each of the primary outcomes in turn (ADAS-Cog, QOL-AD). Secondary analyses will measure outcomes using utility scores generated by the EQ5D and DEMQOL. Bootstrap calculations, will be used for examining the uncertainty in the cost-effectiveness analysis, to provide an estimate of the probability distribution of the ICER, its confidence interval, or variance in the ratio.

We will plot cost-effectiveness acceptability curves (CEACs), which have been widely adopted as a method to quantify and graphically represent uncertainty in economic evaluation studies of health care technologies. They can equally be used in the evaluation of public health interventions. Sensitivity analysis will be undertaken to test whether plausible changes in the values of the main variables affect the results of the analysis.

Cost-consequence analysis is a variant of cost-effectiveness analysis in which the components of incremental costs and consequences (health outcomes) of alternative programmes are listed without aggregation. This analysis will be used for a comparison of secondary outcome measures of participants in the intervention and control arms of the study. The inclusion of a cost-consequence analysis in addition to the standard cost-effectiveness and cost-utility analyses is to set out transparently the full range of costs and consequences resulting from CST so as to assist commissioners and policy makers responsible for funding and coordinating services.

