#### Sample Size

The primary outcome measures are cognition (ADAS-Cog) and quality of life (QoL-AD) at 24 weeks follow up. In the pilot CST trial [6] which recruited people with mild/moderate dementia (MMSE 10-24), community and institutional participants had a similar level of cognitive impairment (mean MMSE 14.5 and 14.1). The RO review [5] found a moderate effect size of 0.58 between the RO and control groups though the studies had some differences in methodology, outcome measures, and length of treatment/follow up. The MCST pilot study found a large effect size of 1.0 compared with CST alone. To detect an effect size for MCST of 0.39 on the ADASCog with power of 80% using a 5% significance level and an estimated attrition of 15% needed, a sample size of 230 at T1 is required. If an estimated 60 participants will have Alzheimer's disease and are suitable/willing to take cholinesterase inhibitors (ACHEIs), this provides sufficient numbers for the maintenance CST/ACHEIs trial platform to estimate effect size and the feasibility of the trial.

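### The protocol allows uncertainty in the primary economic result to be summarised by a variance of the ICER, which does not exist, or by an interval that cannot be read once bootstrap replicates span quadrants

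*Protocol article*

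**What the plan says.** Cost-effectiveness analysis is the primary economic evaluation (Economic evaluation). The next section computes an ICER for ADAS-Cog and another for QoL-AD, and bootstraps them "to provide an estimate of the probability distribution of the ICER, its confidence interval, or variance in the ratio". The three products are alternatives joined by 'or', and each describes the ratio itself.

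The following paragraph makes a further commitment: "We will plot cost-effectiveness acceptability curves (CEACs), which have been widely adopted as a method to quantify and graphically represent uncertainty". Sensitivity analysis is also planned: "Sensitivity analysis will be undertaken to test whether plausible changes in the values of the main variables affect the results of the analysis".

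The same section introduces the ICER as costs relative to outcomes but then defines it "with the denominator being the difference in costs between the intervention and control groups, and the numerator being the difference between these groups" on the chosen outcome. Taken literally, that is effect over cost. Nothing is said about what happens if replicates fall in more than one quadrant.

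On precision, Sample Size targets a standardised effect of 0.39 on the ADAS-Cog at 80% power and 5% significance. For the number to be recruited it gives "an estimated attrition of 15% needed, a sample size of 230 at T1 is required". Allocation at the second randomisation is 1:1 (Randomisation).

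**The concern.** Two of the three named summaries have a known defect.

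- **Variance.** If the denominator is an approximately normal estimate with positive density at zero, the ratio has no finite variance. A bootstrap run still prints a number, but the few replicates nearest zero set its size, and it estimates nothing.
- **Interval.** A negative ratio arises both when maintenance CST is cheaper and better and when it is dearer and worse. A positive ratio arises both when it is dearer and better and when it is cheaper and worse. Once replicates lie in several quadrants, limits on the ratio mix opposite conclusions.

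Both defects exist whichever difference is the denominator, because either can cross zero. If such a summary were published for either primary outcome, it would not describe the uncertainty about cost-effectiveness. The Discussion expects these results to influence provision and guidelines.

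**Working it through.** The document gives no ICER, interval, cost difference or cost SD, so there is no figure of the plan to reproduce. The check is how likely the two failures are at the planned size.

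**Precision of the effect.** Analysed: 230 × 0.85 = 195.5, about 98 per arm. In outcome SD units, with positive values favouring maintenance CST, SE = √(2/98) = 0.143. This ignores clustering, which would raise the SE, and baseline adjustment, which would lower it.

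P(estimate below 0) = Φ(−d/0.143). P(95% CI includes 0) = Φ(1.96 − d/0.143) − Φ(−1.96 − d/0.143).

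| True d | d/SE | P(estimate < 0) | P(95% CI includes 0) |
|---|---|---|---|
| 0.39 (design) | 2.73 | 0.3% | 22% |
| 0.2 | 1.40 | 8.1% | 71% |
| 0.1 | 0.70 | 24% | 89% |
| 0 | 0 | 50% | 95% |

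Under the same normal approximation, the third column is also the share of replicates below zero when d is the observed effect.

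**Assumed costs.** Cost difference 500, with per-person SD of 1,000 or 4,000. SE of the cost difference = SD × 0.143, that is 143 or 571. P(cost difference < 0) = Φ(−500/143) = Φ(−3.5) = 0.02%, or Φ(−500/571) = Φ(−0.875) = 19%. Cost and effect differences were drawn independently from normal distributions, up to 1,000,000 draws.

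**Conventional ratio, cost over effect.** Quadrants are in the order dearer-better / cheaper-better / cheaper-worse / dearer-worse.

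| Observed d | Cost SD | Point ratio | Quadrants (%) | 2.5 to 97.5 percentiles | SD of ratio at 1,000; 5,000; 100,000; 1,000,000 draws |
|---|---|---|---|---|---|
| 0.39 | 1,000 | 500/0.39 = 1,282 | 99.7 / 0 / 0 / 0.3 | 466 to 4,512 | 29,891; 14,016; 25,823; 167,116 |
| 0.39 | 4,000 | 1,282 | 80.8 / 18.9 / 0.1 / 0.3 | −1,968 to 6,850 | 175,715; 78,900; 29,784; 75,172 |
| 0.2 | 1,000 | 500/0.2 = 2,500 | 92.0 / 0 / 0 / 8.0 | −17,957 to 23,311 | 400,159; 202,598; 518,635; 4,833,815 |
| 0.2 | 4,000 | 2,500 | 74.4 / 17.6 / 1.5 / 6.5 | −21,791 to 30,151 | 40,429; 100,275; 960,167; 1,038,632 |

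The SD does not settle in any row, including the first, where only 0.3% of draws have a negative effect. The interval is a usable range in the first row. In the last row its limits combine all four quadrants.

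**Ratio as the article defines it, effect over cost.** At d = 0.39 and cost SD 4,000, the SD over the same numbers of draws was 0.088, 0.073, 0.254 and 0.248, against a point value of 0.39/500 = 0.00078. The percentiles were −0.0070 to 0.0078. At cost SD 1,000 the SD rose from 0.00046 to 0.01285. Inverting the ratio moves the problem to the cost difference and does not remove it.

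**Net benefit from the same draws.** With an assumed 2,000 per SD of effect and cost SD 4,000, net benefit = 2,000 × effect − cost. Its SE is 0.143 × √(2,000² + 4,000²) = 639. At d = 0.39 the point value is 780 − 500 = 280, with simulated 95% limits −973 to 1,530 and probability cost-effective 0.67. At d = 0.2 it is 400 − 500 = −100, with limits −1,352 to 1,153 and probability 0.44. These are finite, ordered and stable.

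**The case against.** The best defence is that a sound expression of uncertainty is already a firm commitment. An acceptability curve gives, at each threshold, the probability that net benefit is positive, which is most of the remedy. The variance is only one of three alternatives, the interval method is not named, and an analysis plan that is not shown could choose well. At the design effect with a clearly positive cost difference, the interval is readable. The cost inputs are all assumed.

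Most of this stands, and it rules out three stronger readings. A reader might infer that the plan has no valid uncertainty measure; the curves contradict that. A reader might infer that a ratio interval is always meaningless; the first simulated row, with 99.7% of draws in one quadrant, contradicts that. A reader might infer that the published error bars will be wrong; the document does not commit to the variance or to the interval, so that does not follow.

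The defence does not rescue the variance option, which fails even under favourable inputs. Nor does it supply a rule for replicates that span quadrants. A valid curve alongside does not make an unstable variance or a mixed interval fit to report.

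**Conclusion.** The point holds as a minor one. The article names a summary, the variance of the ratio, that has no finite value to estimate. It also allows an interval that fails under conditions plausible for this trial: the CI for the effect includes zero in about 22% of trials at the design effect and 71% at about half of it. Those two figures rest on 195.5 analysed, 1:1 allocation and a normal approximation without clustering or covariate adjustment. They are anchored to ADAS-Cog, because no design effect is given for QoL-AD. How often the cost difference crosses zero cannot be known from the document; the assumed inputs gave 0.02% to 19%.

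The planned acceptability curves limit the consequence, and the clinical effectiveness analysis is not affected. Separately, the ICER definition contradicts itself within one sentence. That needs no assumed input to establish.

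**What to change.** In Incremental Cost-effectiveness Analysis:

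1. Delete the variance of the ratio from the list of bootstrap outputs.
2. Keep the point ICER. Report a confidence interval for it only when essentially all replicates lie in one quadrant, with the cut-off set in advance.
3. Otherwise, rest the uncertainty statement on the bootstrap cost-effectiveness plane, the planned acceptability curve, and incremental net benefit (willingness to pay × effect difference − cost difference) with a 95% CI over a stated willingness-to-pay range for each outcome.
4. In the same edit, make the ICER definition consistent, so that the description as costs relative to outcomes and the placing of numerator and denominator agree.

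The cost is a few lines of text. The same replicates serve, with no new data or participants. The willingness-to-pay ranges per ADAS-Cog point and per QoL-AD point have to be chosen, since the article gives none. The downside is that results appear over a range of willingness to pay instead of as one interval.

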## Discussion

This innovative and pragmatic RCT that evaluates the effectiveness and cost-effectiveness of a maintenance CST programme for dementia constitutes one of the largest and longest trials for people with dementia and one of the first including an integrated cost-effective analysis of a psychosocial intervention. This study reflects the current emphasis on improving cognition and quality of life using psychosocial interventions, and the emphasis is on working under a person-centred framework through group exercises aiming at global stimulation of cognitive abilities for a prolonged period of time. The NICE-SCIE guidelines [8] on the management of dementia offer few evidence-based recommendations about psychosocial approaches. This is mainly due to the lack of high-quality studies showing their efficacy and lack of specific guidance for the duration that psychosocial interventions should be provided. The results of this trial may therefore contribute to future practice guidelines and, if successful, will help the widespread use of psychosocial interventions in dementia care such as CST within health and social care services [38]. CST has now been evaluated in a number of countries [21,39,40] and the UK National Audit Office report highlighted that CST was available in 29% of community mental health teams for older people [41].

This study should provide definitive evidence of the potential efficacy of maintenance CST and establish how far the long-term efficacy can be compared with antidementia drugs such as cholinesterase inhibitors in terms of cognition and quality of life. The results of this study, both in terms of efficacy and cost-effectiveness, are likely to influence the availability and provision of maintenance CST in the UK and internationally, and will also impact on evidence-based guidelines and strategic policies in dementia care.

## Appendix 1

### Inclusion and exclusion criteria

#### Inclusion criteria

All participants are people with dementia who:

◦ meet the DSM-IV criteria for dementia of any type, including Alzheimer's, vascular, Lewy Body type and mixed

◦ are in the mild to moderate stage of dementia (Clinical Dementia Rating)

◦ can communicate and understand communication in English

◦ can engage in group activity for at least 45 minutes

#### Exclusion criteria

Participants do not have any characteristic which could affect participation, e.g.: major physical illness; sensory impairment; disability or high level of agitation.
